# Hit hard and early: analysing the effects of high-dose methylprednisolone on nailfold capillary changes and biomarkers in very early systemic sclerosis: study protocol for a 12-week randomised controlled trial

**DOI:** 10.1186/s13063-018-2798-x

**Published:** 2018-08-22

**Keywords:** Systemic sclerosis, Methylprednisolone, Randomised controlled trial, Very early diagnosis of systemic sclerosis, Nailfold capillaroscopy

## Abstract

**Background:**

Mounting evidence indicates that inflammatory mechanisms drive systemic sclerosis (SSc) vasculopathy and fibrosis, especially early in the disease. Therefore, patients with very early SSc could benefit from early treatments targeting inflammation. Glucocorticoids are among the most potent anti-inflammatory and immunosuppressive agents. Several studies have demonstrated a mixed response to treatment with glucocorticoids in SSc, probably because it is seldom initiated at very early stages of the disease. We hypothesise that by inhibiting the inflammatory process driving SSc disease progression, glucocorticoid treatments will induce remission in patients with very early SSc.

**Methods/design:**

This study is a 12-week, randomised, double-blind, placebo-controlled trial analysing the effects of high-dose intravenous methylprednisolone in very early SSc. Thirty patients who fulfil the criteria for very early SSc will be randomly assigned in a 2:1 ratio to receive either intravenous methylprednisolone or a placebo on three consecutive days over three consecutive months. In this study, the primary endpoint will be the change in capillary density between the baseline and after 12 weeks of treatment. The secondary outcomes of this study are a change in selected biomarkers, other changes in the nailfold capillaries, signs of established SSc and changes in physical function, general health and utilities, as reported through questionnaires.

**Discussion:**

This trial is the first aiming to treat very early SSc and is promising because it targets the very early stages of the disease process by using an inexpensive and relatively safe treatment known to be highly effective against inflammation. The use of vasculopathy and inflammatory biomarkers as well as clinical signs and symptoms as the endpoints in our study enables us to meet the patient need for markers of disease activity. If it is possible to prevent clinically significant disease in patients with very early SSc by using a safe treatment, this will cause a paradigm shift in scleroderma care and research.

**Trial registration:**

ClinicalTrials.gov Identifier: NCT03059979. Registered on 20 February 2017.

**Electronic supplementary material:**

The online version of this article (10.1186/s13063-018-2798-x) contains supplementary material, which is available to authorized users.

## Background

In systemic sclerosis (SSc), the extent of organ involvement largely determines patient quality of life and disease burden. Organ involvement often occurs in the first three years of the disease and is tightly linked to an increase in mortality, decreasing the 5-year survival rate to 84% to 91%. To date, no treatment is available to cure SSc and its aetiology is unknown [1]. The major pathogenic features of SSc are a dysregulation of the immune system, dysfunction of the vasculature, and the activation of fibroblasts and other resident cells. Several studies have indicated that inflammatory mechanisms drive SSc vasculopathy and fibrosis, especially at the early stages of the disease [2–7].

In addition, it is likely that SSc shares an autoimmune inflammatory basis with other systemic autoimmune diseases such as lupus nephritis [8]. Glucocorticoids, some of the most potent anti-inflammatory and immunosuppressive agents, can induce remission in systemic autoimmune diseases, including lupus nephritis and dermatomyositis, and have an immediate and profound effect on the trafficking of leucocytes [9–11]. Furthermore, glucocorticoids affect both T- and B-lymphocytes.

A systematic review on the use of glucocorticoids in treating SSc showed conflicting results in skin and lung involvement but positive effects on myopathy [12]. The partially poor clinical response to glucocorticoid treatment in SSc might result from delays in its application, meaning that it cannot prevent the very early induction of vasculopathy and fibrosis arising as a result of inflammation [1, 13–15].

The European League Against Rheumatism (EULAR) Scleroderma Trials and Research Group has identified preliminary criteria for the very early diagnosis of systemic sclerosis (VEDOSS), which include the combination of Raynaud’s phenomenon, disease-specific auto-antibodies, typical nailfold capillaroscopic findings and “puffy fingers” [16, 17].

Recent developments in our understanding of the overlapping disease mechanisms of SSc and other autoimmune diseases, the inflammatory mechanisms involved in early SSc and the partial response of SSc treated with glucocorticoids suggest a possible treatment opportunity in patients with early SSc. The aim of this trial is to examine the effects of high-dose glucocorticoids on the inhibition of the inflammatory process in very early SSc.

## Methods/design

This 12-week, double-blind, randomised, placebo-controlled trial is under way (inclusion began on January 1, 2017, and is open until July 1, 2018) at the Department of Rheumatology of Radboud University Medical Centre in Nijmegen, The Netherlands.

### Objectives

The aim of this study is to analyse whether high-dose methylprednisolone has an effect on very early SSc in terms of nailfold capillaromicroscopy (NCM) abnormalities, SSc signs and symptoms, and inflammation biomarkers. This led to the following research questions.

### Primary objective

The purpose of this study was to determine the effect of short-term treatment with high-dose glucocorticoids on vasculopathic abnormalities, as measured by using NCM in patients with very early SSc.

### Secondary objectives

The key secondary objective is to determine the effects of the short-term treatment of SSc with high-dose glucocorticoids on changes in the following:the signs and symptoms of disease progression,inflammation biomarkers, andgeneral health and utilities, as measured by standardised questionnaires.

### Study design rationale

In order to investigate the effect of high-dose methylprednisolone in very early SSc, we have designed a randomised, placebo-controlled, double-blind, mono-centre superiority trial with a primary endpoint of changes in nailfold capillary density after 12 weeks. Randomisation will be performed in blocks of six after the stratification of anti-centromere/anti-topoisomerase auto-antibodies, sex and age and there will be a 2:1 patient allocation to groups receiving intravenous methylprednisolone or placebo.

### Study outcome rationale

In SSc, the outcome measures of interventions are not extensively available. The most accepted outcome measure is a change in skin involvement, measured by using the modified Rodnan skin score (mRSS). However, in our study population of patients with very early SSc, the mRSS is 0 by definition at the outset. Nailfold capillary abnormalities have been identified as a symptom for diagnosing early SSc and are included in the American College of Rheumatology/EULAR (ACR/EULAR) classification criteria for SSc. Nailfold capillary abnormalities are evaluated by using NCM. The typical changes of the nailfold capillaries during SSc consist of the appearance of the following capillaroscopic hallmarks: the presence of enlarged or giant capillaries, haemorrhages, loss of capillaries, disorganisation of the microvascular array, and capillary ramifications. Semi-qualitative rating scores, especially of capillary density, have value in predicting the occurrence of organ involvement and mortality in SSc [18]. To date, the effect of immunosuppressant drugs on the nailfold capillaries in SSc has not been extensively studied. The most successful treatment of progressive SSc to date involved an autologous haematopoietic stem cell transplantation (ASCT), after which microcirculation estimated by using NCM was reported to be improved in separate studies [19, 20]. In patients who received ASCT, an improved capillary density was observed just 3 months after treatment and persisted during follow-ups over 24 months while no NCM modification was detected in patients who received cyclophosphamide [20]. In early SSc, the presence of giant capillaries is the dominant NCM feature, which can entail a decreased capillary density [21].

### Participants, intervention and outcomes

#### Inclusion criteria

Patients who meet the following criteria at randomisation are eligible for the study:age of more than 18 years,fulfil VEDOSS criteria [16]: Raynaud’s phenomenon AND positive test for anti-centromere or anti-topoisomerase antibodies AND nailfold capillaroscopic findings typical of SSc,puffy fingers for less than 3 years, andmRSS of 0.

#### Exclusion criteria

Patients who, at randomisation, meet any of the following criteria are not eligible for the study:presence of acrosclerosis, acro-osteolysis or digital ulcers,presence of anti-RNA polymerase III auto-antibodies,previous systemic treatment for SSc, namely methotrexate, prednisone (>14 days in the previous 6 months), mycophenolate mofetyl or cyclophosphamide,clinically significant internal organ involvement: diffusing capacity for carbon monoxide (DLCO) less than 80% predicted, vital capacity less than 70% predicted, renal dysfunction with glomerular filtration rate less than 60 mL/min, diastolic dysfunction more than grade 1 on echocardiography, pulmonary hypertension, or weight loss more than 10% in the last 6 months with unknown cause, andcontra-indications for methylprednisolone.

### Intervention

#### Investigational product/treatment

Eligible patients will be randomly assigned to groups, receiving either a daily infusion of methylprednisolone (1000 mg) or a placebo (physiologic salt solution identical in appearance) on three consecutive days in three consecutive months. The study drug and placebo will be provided by the local hospital pharmacy. Infusions will be given at the outpatient facilities of the rheumatology department.

#### Use of co-medication

All patients will receive prophylactic therapy with an angiotensin-converting enzyme inhibitor and a proton-pump inhibitor for the duration of the study. Treatment with other systemic therapies for SSc symptoms will be avoided whenever possible during the study and will be regarded as a protocol violation.

#### Follow-up treatment

After the 12-week assessment, patients will usually receive no treatment, as is the standard care in very early SSc. However, methotrexate (25 mg per week) can be started if a patient develops limited skin involvement but no significant internal organ involvement. Intravenous pulses of cyclophosphamide or mycophenolate mofetil can be started if a patient has rapidly evolving skin involvement or if signs of significant internal organ involvement are present or if both occur.

#### Escape treatment

In case of the significant worsening of symptoms (development of diffuse skin involvement, weight loss of more than 10%, or the occurrence of significant internal organ involvement), the treatment with methylprednisolone will be stopped and an appropriate treatment will be started in accordance with the EULAR treatment recommendations for SSc [22].

### Outcome measures

#### Primary outcome

In this study, the primary endpoint will be the change in capillary density between the baseline and after 12 weeks of treatment.

#### Secondary outcomes

The secondary outcomes (all compared between the baseline and week 12 or between the baseline and 1 year) of this study are (a change in):selected biomarkers: the interferon signature in peripheral blood cells, CXCL4, interleukin-1 beta (IL-1β), IL-6, tumor necrosis factor-alpha (TNF-α), ET-1, intercellular adhesion molecule 1 (ICAM-1) and vascular endothelial growth factor (VEGF) [3, 23–27];nailfold capillary changes other than capillary density and the presence of giant capillariesan mRSS; the presence of puffy fingers; the presence of synovitis; the presence of tendon friction rubs; fulfilling EULAR/ACR classification criteria for SSc [28];pulmonary function tests; the presence of interstitial lung disease; a suspicion of pulmonary hypertension; andphysical function, general health and utilities as measured by the Scleroderma Health Assessment Questionnaire (SHAQ), 36-Item Short Form Health Survey (SF-36), EuroQOL five dimensions questionnaire (EQ5D) and Gastrointestinal Tract Questionnaire (GIT).

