### Statistical analysis

The data will be analysed primarily according to the intention-to-treat principle. Missing values due to participant drop-out are treated according to the last observation carried forward. A *P* value of 0.05 will be used to denote statistical significance for between-group differences in the primary outcome.

Between-group differences in the change in efficacy outcome variables between the baseline and week 12 will be analysed by using an analysis of covariance or logistical regression. Similarly, the ongoing changes to the continuous outcomes will be analysed between the baseline and weeks 4, 8 and 12 by using a repeated-measures analysis of variance.

Serious and minor adverse events will be tabulated by group, and depending on the occurrence, a time-to-event analysis may be used to analyse between-group differences in serious adverse events. The use of any immunosuppressive therapy between week 12 and the 1-year follow-up will be described for each of the two groups.

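### The 1-year comparison of reversible progression signs is read after immunosuppressants may have been started for those same signs, so it does not show whether progression was prevented

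*Protocol article*

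**What the plan says.** Under Secondary objectives, the key secondary objective includes the effect of treatment on "the signs and symptoms of disease progression". Inclusion criteria require "puffy fingers for less than 3 years, andmRSS of 0", and Exclusion criteria remove patients with clinically significant organ involvement. New skin or organ disease is therefore a first event.

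Secondary outcomes lists mRSS, "the presence of puffy fingers; the presence of synovitis; the presence of tendon friction rubs; fulfilling EULAR/ACR classification criteria for SSc", and "pulmonary function tests; the presence of interstitial lung disease; a suspicion of pulmonary hypertension". These are "all compared between the baseline and week 12 or between the baseline and 1 year", as change or presence. Assessments places visits at months 1, 2, 3, 6, 9 and 12.

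Follow-up treatment states: "After the 12-week assessment, patients will usually receive no treatment, as is the standard care in very early SSc". It then gives exceptions triggered by worsening. One is that "methotrexate (25 mg per week) can be started if a patient develops limited skin involvement but no significant internal organ involvement". Cyclophosphamide or mycophenolate is allowed for rapidly evolving skin disease or organ involvement. Escape treatment stops methylprednisolone and starts other treatment on significant worsening.

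Statistical analysis names intention-to-treat, last observation carried forward for drop-out, and ANCOVA or logistic regression for baseline to week 12. On later drugs it says: "The use of any immunosuppressive therapy between week 12 and the 1-year follow-up will be described for each of the two groups".

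**The concern.** The trigger for the later drugs is the appearance of what the 1-year outcome measures. Suppose a placebo patient develops skin involvement at month 5, starts an immunosuppressant and is back at mRSS 0 at month 12. That patient is recorded as unchanged, exactly like a patient who never progressed. If methylprednisolone prevents progression, more placebo than active patients will reach a trigger, so later treatment removes more of the placebo arm's events.

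The Abstract and Discussion present the goal as preventing clinically significant disease. A reading at 1 year, taken regardless of what was started in between, answers a different question: how patients fare under a policy of early methylprednisolone or placebo followed by treatment as needed. The description of immunosuppressant use can reveal an imbalance but does not bring it into the comparison. It also starts at week 12, so escape treatment begun before then falls outside it.

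**Working it through.** **The plan's own figure.** The only design calculation concerns the week-12 primary outcome. The detectable difference is (1.960 + 0.842) × 0.9 × √(1/10 + 1/20) = 0.977, which agrees with the stated value of nearly 1.0. It says nothing about the 1-year outcomes, for which the article gives no progression, treatment or reversal rates. Every rate below is an assumption.

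**Model.** Let p be the proportion who ever progress by 1 year, s the share of progressors started on immunosuppressants, and q the share of those who no longer show the sign at month 12. Then

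proportion with the sign at month 12 = p × (1 − k), where k = s × q.

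With the same k in both arms, the risk difference is multiplied by (1 − k) and the risk ratio is unchanged.

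**Equal k in both arms (placebo v methylprednisolone)**

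| Ever progressed | k | Seen at month 12 | Risk difference (points) | Risk ratio | Odds ratio | Loss in log-odds ratio |
|---|---|---|---|---|---|---|
| 40% v 15% | 0 | 40% v 15% | 25 | 0.375 | 0.265 | – |
| | 0.30 | 28% v 10.5% | 17.5 | 0.375 | 0.302 | 10% |
| | 0.50 | 20% v 7.5% | 12.5 | 0.375 | 0.324 | 15% |
| 30% v 10% | 0 | 30% v 10% | 20 | 0.333 | 0.259 | – |
| | 0.30 | 21% v 7% | 14 | 0.333 | 0.283 | 7% |
| | 0.50 | 15% v 5% | 10 | 0.333 | 0.298 | 10% |
| 50% v 20% | 0 | 50% v 20% | 30 | 0.40 | 0.250 | – |
| | 0.6 × 0.25 = 0.15 | 42.5% v 17% | 25.5 | 0.40 | 0.277 | 7% |
| | 0.8 × 0.5 = 0.40 | 30% v 12% | 18 | 0.40 | 0.318 | 17% |
| | 1.0 × 0.75 = 0.75 | 12.5% v 5% | 7.5 | 0.40 | 0.368 | 28% |

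Example: for 40% v 15% the odds ratio is (0.15/0.85)/(0.40/0.60) = 0.265. At k = 0.30 it is (0.105/0.895)/(0.28/0.72) = 0.302. The log-odds loss is 1 − ln 0.302/ln 0.265 = 10%.

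**Unequal treatment of progressors (50% v 20%, q = 0.5)**
- 80% of placebo and 40% of active progressors treated: 0.50 × 0.60 = 30% v 0.20 × 0.80 = 16%. The difference is 14 points, and the risk ratio moves from 0.40 to 0.53.
- The reverse, 40% and 80%: 0.50 × 0.80 = 40% v 0.20 × 0.60 = 12%. The difference is 28 points and the risk ratio is 0.30, so the relative effect is overstated.

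**Precision.** With 10 placebo and 20 active patients, exact two-sided Fisher power at k = 0 is about 34% for 50% v 20%, 28% for 40% v 15% and 23% for 30% v 10%. For 50% v 20% it falls to about 28%, 18% and 5% at k = 0.15, 0.40 and 0.75. The comparison is one of estimation in any case.

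**The case against.** Four points on the other side carry weight.

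- **The 1-year comparison is legitimate as it stands.** Under intention-to-treat it validly contrasts two policies, and the per-group description would expose excess drug use on placebo. This stands: the reading is incomplete for the prevention aim, not invalid.
- **The objective need not rest on 1 year.** The objective concerns short-term treatment, the stated models run to week 12, and the 0.05 threshold is given for the primary outcome only. The week-12 comparison precedes all follow-up treatment; only escape treatment can touch it. This limits the importance of the point. Handling of later drugs could sit in an analysis plan that is not shown, but the outcome definition is fixed in the article.
- **The effect is easily overstated.** A reader might infer that 30% to 50% of a real benefit is lost, or that the effect is driven towards zero. The documents do not support this. That loss is the assumed k returned on the risk-difference scale. It needs many progressors to be treated and reversed, whereas the article says drugs may be started and that no treatment is usual. On the logistic scale, the method the article names for binary outcomes, the loss is much smaller, and the risk ratio may not move at all. Lasting findings such as established interstitial lung disease are less exposed.
- **A first-event outcome has its own noise.** A single small mRSS reading could become a permanent event in either arm. A reader might also suppose that events seen at months 6 and 9 are being discarded, but the schedule of items by visit is in Fig. 1, which is not shown.

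**Conclusion.** The point holds as a modest design improvement. For signs that treatment can reverse (mRSS, puffy fingers, synovitis, friction rubs, lung function), the 1-year reading follows treatment that may have been chosen because of the outcome, and the stated handling is description only. It therefore cannot separate progression prevented from progression treated. The likely direction, if the drug works, is understatement; the opposite imbalance in drug use could overstate the relative effect.

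The size cannot be derived from the documents. Under the assumed rates the risk difference loses about 15% to 50% in mild to moderate cases, in proportion to the share both treated and reversed. The log-odds ratio loses about 7% to 15% at 40% v 15% and 30% v 10% with k of 0.30 to 0.50 (7% to 17% at 50% v 20% with k of 0.15 to 0.40). The risk ratio is unaffected when both arms are treated and reverse alike. The week-12 primary outcome is not in question here.

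**What to change.** Add a secondary outcome, progression by 1 year. Count as an event the first of:
- skin involvement at any visit where mRSS is already scheduled;
- significant organ involvement at any visit where the relevant assessment is already scheduled;
- immunosuppression started for worsening under the triggers already written in Follow-up treatment and Escape treatment, including escape before week 12.

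Compare the arms on the proportion with an event or the time to the first event. Give estimates with confidence intervals rather than rely on a test, as there are only 20 v 10 patients. Report the month-12 scores alongside, labelled as including the effect of later treatment.

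The cost is mainly wording in the outcome and analysis sections. Drug use from week 12 to 1 year must be reported already; the addition is to record the start date and reason, and to cover the first 12 weeks. The downside is that starting a drug is partly the physician's judgement and a small isolated mRSS reading may be a false event, so show the components separately. No treatment rule changes.

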### Assessments

Regular visits are planned at the baseline and after months 1, 2, 3, 6, 9 and 12. See Fig. 1—according to the Additional file 1: SPIRIT (Standard Protocol Items: Recommendations for Interventional Trials) checklist—for an overview of all visits and assessments.

**Fig. 1 Fig1:**
[figure not shown]
Study visits and procedures. Pulmonary function tests consisting of vital capacity, total lung capacity and carbon monoxide (CO) diffusion capacity. Plasma biomarkers consist of CXCL4, interleukin-1 beta (IL-1β), tumor necrosis factor alpha (TNFα), IL-6, ET-1, intercellular adhesion molecule 1 (ICAM-1) and vascular endothelial growth factor (VEGF). Abbreviation: *HRCT* high-resolution computer tomography

### Sample size

The effect of high-dose methylprednisolone on nailfold capillary changes and other outcomes in early SSc is unknown; therefore, the optimal size of a pilot trial is unknown. If the sample is too small, the estimate of the effect will be too uncertain. If the sample is too large, it may be judged as unnecessarily exposing participants to risks and burdens and therefore as being unethical. Furthermore, setting the sample size too high may lead to a preventable failure to reach the recruitment target. To minimise the risk for participants and maximise the information gained, we judged that the inclusion of 30 patients (20 in the treatment arm and 10 in the placebo arm) would be appropriate for this pilot study. When adopting the usual alpha of 0.05, power of 0.80, standard deviation of 0.9 and randomisation scheme of 2:1, a between-group difference of nearly 1.0 in the capillary density score thus would represent a statistically significant difference, using the standard sample size formula. In previous ASCT treatments for SSc, the change in capillary density over the first 12 weeks was 1.5 in the intervention group, and there was no change in the control group [20]. Patients are randomly assigned at a 2:1 ratio to maximise the information about the experimental intervention, which can be justified as the risks of the intervention are known and relatively low.

